## Abstract

**Background:**

Acute mesenteric ischaemia (AMI) is a life-threatening disease where early diagnosis is critical to avoid morbidity and mortality from extensive irreversible bowel necrosis. Appropriate prediction of presence of bowel necrosis is currently not available but would help to choose the optimal method of treatment.

The study aims to identify combinations of biomarkers that can reliably identify AMI and distinguish between potentially reversible and irreversible bowel ischaemia.

**Methods:**

This is a prospective multicentre study. Adult patients with clinical suspicion of AMI (*n* = 250) will be included. Blood will be sampled on admission, at and after interventions, or during the first 48 h of suspicion of AMI if no intervention undertaken. Samples will be collected and the following serum or plasma biomarkers measured at Tartu University Hospital laboratory: intestinal fatty acid-binding protein (I-FABP), alpha-glutathione S-transferase (Alpha- GST), interleukin 6 (IL-6), procalcitonin (PCT), ischaemia-modified albumin (IMA), D-lactate, D-dimer, signal peptide-CUB-EGF domain-containing protein 1 (SCUBE-1) and lipopolysaccharide-binding protein (LBP). Additionally, more common laboratory markers will be measured in routine clinical practice at study sites.

Diagnosis of AMI will be confirmed by computed tomography angiography, surgery, endoscopy or autopsy.

Student’s t or Wilcoxon rank tests will be used for comparisons between transmural vs. suspected (but not confirmed) AMI (comparison A), confirmed AMI of any stage vs suspected AMI (comparison B) and non-transmural AMI vs transmural AMI (comparison C). Optimal cut-off values for each comparison will be identified based on the AUROC analysis and likelihood ratios calculated. Positive likelihood ratio > 10 (> 5) and negative likelihood ratio < 0.1 (< 0.2) indicate high (moderate) diagnostic accuracy, respectively. All biomarkers with at least moderate accuracy will be entered as binary covariates (using the best cutoffs) into the multivariable stepwise regression analysis to identify the best combination of biomarkers for all comparisons separately. The best models for each comparison will be used to construct a practical score to distinguish between no AMI, non-transmural AMI and transmural AMI.

**Discussion:**

As a result of this study, we aim to propose a score including set of biomarkers that can be used for diagnosis and decision-making in patients with suspected AMI.

**Trial registration:**

NCT06212921 (Registration Date 19–01-2024).

**Supplementary Information:**

The online version contains supplementary material available at 10.1186/s12893-024-02491-3.

## Background

Acute mesenteric ischaemia (AMI) is a rare disease, difficult to diagnose due to lack of specific symptoms and reliable biomarkers [1]. Early diagnosis is crucial to avoid extensive irreversible bowel injury resulting in severe disability due to short bowel syndrome, or death. Despite availability of computed tomography (CT), vascular surgery and interventional radiology the mortality of AMI remains very high [2, 3]. While CT angiography is the gold standard of diagnosis of occlusive AMI, non-occlusive AMI (NOMI) has less distinctive CT signs [1]. Neither clinical symptoms nor CT scan perform well in any subtype of AMI in predicting whether bowel ischaemia is transmural or not, while this assessment is extremely important for choosing treatment method (endovascular revascularization vs open surgical approach).

A recent systematic review revealed no biomarker with high accuracy in diagnosis of AMI [4]. Several shortcomings in the existing literature were identified in this review: (1) Patients with strangulating bowel obstruction were included in most of the studies and the severity of ischaemia was seldom specified; (2) Biomarkers were commonly measured only once, with the measurement time point falling in different periods after occurrence of symptoms; (3) Combinations of biomarkers were rarely assessed; (4) Severity of bowel injury (non-transmural vs. transmural ischaemia) was not reported in many studies; (5) Reperfusion was not considered in any of the studies. Accordingly, we believe that biomarkers related to those sub-types have not been sufficiently studied, giving a rationale for this study.

There are obvious differences in pathophysiological mechanisms between different sub-types of AMI, whereas differences and similarities regarding biomarkers have not been studied.

Serum inflammatory markers interleukin-6 (IL-6) and procalcitonin (PCT), ischaemia modified albumin (IMA) and alpha-glutathione S transferase (alpha-GST) have shown relatively high predictive values for diagnosis of any type (transmural or not transmural) of AMI in humans [4]. Of coagulation factors, D-dimers performed moderately well in predicting transmural AMI in humans [4], while signal peptide-CUB-EGF domain-containing protein 1 (SCUBE-1) predicted early mesenteric ischaemia in animal experiments [5, 6]. The enterocyte injury marker intestinal fatty acid-binding protein (I-FABP) has been extensively studied in humans and has shown moderate diagnostic accuracy for diagnosis of AMI [4]. While D-lactate performed relatively poorly as a biomarker for AMI in humans [4], animal studies have shown promising results [7–9], also including intestinal barrier dysfunction markers like D-lactate and lipopolysaccharide binding protein (LBP) in potential combinations may lead to improved diagnostic accuracy.

Numerous animal studies have shown potential of different biomarkers in diagnosis of AMI but results in animal models with clear-cut onset are not easy to transfer to humans [5–11].

Non-occlusive mesenteric ischaemia (NOMI) and mesenteric venous thrombosis are difficult to study in animal models. Moreover, observation period after experimental AMI is usually short, and ischaemia and reperfusion periods commonly not distinguished. Human studies considering time of ischaemia and subsequent severity of intestinal injury are lacking, as well as studies assessing biomarker dynamics during reperfusion after successful revascularisation.

Different biomarker combinations may be optimal for different sub-types and severity of AMI, and for different time points of measurement after onset of symptoms.

The current study will be undertaken to identify combinations of biomarkers that can reliably identify AMI when compared to suspected but not confirmed AMI, ideally allowing to distinguish between non-transmural and transmural bowel damage. We aim to propose a practical score for clinical decision-making.

## Methods

### Objectives

#### Primary objective:

To identify a combination of biomarkers that distinguishes patients with transmural AMI from patients with no AMI with a positive likelihood ratio of > 10 and negative likelihood ratio of < 0.1 at least at one measurement time point before any treatment of AMI (comparison A).

#### Secondary objectives:

To identify a combination of biomarkers that distinguishes patients with AMI (any stage—non-transmural or transmural necrosis) from patients with no AMI with positive likelihood ratio of > 10 and negative likelihood ratio < 0.1 at least at one measurement time point before any treatment of AMI (comparison B).To identify combination of biomarkers that distinguishes patients with non-transmural AMI from patients with transmural AMI with positive likelihood ratio of > 5 and negative likelihood ratio < 0.2 at at least one measurement time point before any treatment of AMI (comparison C).

#### Tertiary objectives:

To assess performance of identified biomarker combinations in different subtypes of AMI (arterial occlusive, NOMI, mesenteric venous thrombosis)To describe patterns of individual biomarkers before and after treatment of AMI, separating between ongoing ischaemia and reperfusion.

### Study design and eligibility criteria

This is a prospective multicentre study.

All adult patients with clinical suspicion of acute mesenteric ischaemia will be considered eligible for the study.

#### Inclusion criteria

Age 18 years or older.

Initial decision in favour of further diagnostics of mesenteric ischaemia.

#### Exclusion criteria

Age < 18 years.

Consent declined or withdrawn by patient or next of kin.

Chronic mesenteric ischaemia without an acute event.

Immediate decision for withdrawal of further diagnostic workup and active treatment.

Referral from another hospital more than 8 h after diagnosis of AMI.

Strangulated bowel obstruction (SBO) as a primary verified diagnosis.

AMI incidentally diagnosed at surgery without previously having been considered.

### Definitions

#### Suspicion of AMI will be defined as:

Clinical suspicion of AMI. Factors indicating AMI are (not limited to): abdominal pain (usually diffuse and strong) usually supported with appropriate phenotype for AMI (older age, atrial fibrillation) and absence of an obvious alternative diagnosis after primary clinical assessment.Clinical suspicion of mesenteric venous thrombosis. Unspecific and less intense abdominal pain, risk factors for venous thrombosis (mainly thrombophilia and obesity).Clinical suspicion of NOMI (distended abdomen, ileus or unexplained worsening of shock) in critically ill patients with hypoperfusion and/or hypotension, often receiving vasopressors.

#### Confirmed AMI will be defined as:

Total or subtotal occlusion of any large mesenteric vessel visualized on CT, magnetic resonance imaging (MRI) or plain angiography with acute symptoms (e.g. abdominal pain, diarrhoea, shock, mucosal sloughing).Imaging finding without any symptoms of intestinal ischaemia and without any laboratory abnormalities is not sufficient to confirm AMI (probably indicating chronic mesenteric ischaemia). For definitive confirmation in such case either endoscopic finding of mucosal ischaemia, surgical finding of transmural ischaemia leading to resection or palliation, or autopsy finding of any stage of bowel ischaemia is needed to confirm the diagnosis.Non-occlusive mesenteric ischaemia confirmed by either endoscopy, surgery or autopsy. A suspicion of NOMI in CT, MRI or angiography without being confirmed by any of these methods remains a suspicion of AMI.

Each case without definitive confirmation of AMI or without definitive confirmation of the subtype of AMI will be carefully reviewed by steering committee members and discussed with respective site to confirm the final categorization.

Patients with strangulating bowel obstruction (SBO) as an immediate verified diagnosis at the time of the first clinical assessment will be excluded from this study. If a SBO was identified as a cause of AMI only after including the patient in the study (as suspected AMI), this patient should continue in the study.

Patients with acute-on-chronic mesenteric ischaemia will be included.

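### The confirmation rule for occlusive AMI can count an old mesenteric occlusion with acute symptoms from another cause as a confirmed case

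*Protocol article*

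**What the plan says.** Under the heading on confirmed AMI, the protocol article accepts as confirmation "Total or subtotal occlusion of any large mesenteric vessel visualized on CT, magnetic resonance imaging (MRI) or plain angiography with acute symptoms". The examples of symptoms are "e.g. abdominal pain, diarrhoea, shock, mucosal sloughing". A caveat follows: "Imaging finding without any symptoms of intestinal ischaemia and without any laboratory abnormalities is not sufficient to confirm AMI". Only in that situation does an occlusive case need further proof from endoscopy, surgery or autopsy. NOMI always needs proof by one of those three routes.

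Entry works as follows. The formal inclusion criterion is "Initial decision in favour of further diagnostics of mesenteric ischaemia". The definition of suspicion begins "Factors indicating AMI are (not limited to): abdominal pain (usually diffuse and strong", and it adds "absence of an obvious alternative diagnosis after primary clinical assessment". For NOMI it names a distended abdomen, ileus or worsening shock.

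Three other provisions bear on the point:
- The exclusion criteria remove "Chronic mesenteric ischaemia without an acute event", while acute-on-chronic disease is deliberately included.
- At least one study investigator validates inclusion, confirmation and subtype.
- The steering committee reviews cases in which AMI or its subtype is not definitively confirmed, and cases of unclear or unusual mechanism.

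**The concern.** The rule has an imaging half and a symptom half. The symptom half separates few patients, because most were enrolled with the kind of symptom that satisfies it. For a symptomatic patient, confirmation then rests largely on a total or subtotal occlusion being visible. Nothing in the rule asks whether the occlusion is new, whether the bowel shows ischaemia, or whether another diagnosis explains the symptoms.

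The caveat shows that the authors foresaw chronic occlusion, but it acts only when two conditions hold together. Patients under suspicion of AMI seldom have no symptoms. The sites are also asked for lactate, white cells, CRP, creatinine and troponin at the first time point, so a wholly normal panel will be uncommon as well.

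The label is the reference standard for every accuracy figure. A patient without acute ischaemia who is labelled confirmed moves from the no-AMI group to the AMI group, most probably as non-transmural because no necrosis is found. In comparison B this lowers observed sensitivity and raises LR-. In comparison C it mixes non-ischaemic patients into the non-transmural arm. The three-category score inherits both errors.

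**Working it through.** **Does any stated safeguard reach the patient in question?** Take a patient with an old subtotal occlusion and acute abdominal pain from another cause.

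| Provision | Does it reach this patient? |
|---|---|
| Caveat inside the definition | No. Pain is present, and one abnormal laboratory value would also switch the caveat off. |
| Exclusion of chronic ischaemia | Possibly. The article does not say how an acute event is told from unrelated pain. |
| No obvious alternative diagnosis | Partly. It is a factor in suspicion, judged at primary assessment; a diagnosis made later does not undo confirmation. |
| Investigator validation | Possibly, but the validator applies this same definition. |
| Steering committee | Only if subtype or mechanism is unclear. As to AMI itself, the case already counts as confirmed. |

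So the patient can be counted as confirmed, and whether that happens depends on individual judgement.

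**How much could it matter in comparison B?** The article gives no figure to reproduce here, so this is an illustration.

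Inputs from the article: 160 confirmed cases (40 of them NOMI, so 160 − 40 = 120 occlusive), 90 patients without confirmed AMI, and the target LR- < 0.1.

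Assumptions: a share q of 5, 10 or 20% of the 90 is mislabelled; these patients test like other patients without AMI; no safeguard stops any of them; true specificity (Sp) is 0.95; true sensitivity (Se) is 0.95 or 0.93.

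Formulas, with k = 90 × q:
- observed sensitivity = (160 × Se + k × (1 − Sp)) / (160 + k)
- LR- = (1 − observed sensitivity) / Sp

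Example for Se 0.95 and q = 10%: k = 9; (152 + 0.45) / 169 = 0.902; LR- = 0.098 / 0.95 = 0.103.

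| q | k | LR-, Se 0.95 | LR-, Se 0.93 |
|---|---|---|---|
| 0% | 0 | 0.053 | 0.074 |
| 5% | 4.5 | 0.079 | 0.099 |
| 10% | 9 | 0.103 | 0.123 |
| 20% | 18 | 0.148 | 0.167 |

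Setting LR- to 0.1 and solving gives k = 160 × (Se − 0.905) / 0.855. That is 8.4 patients for Se 0.95 (9.4% of 90) and 4.7 patients for Se 0.93 (5.2% of 90). LR+ barely moves: for Se 0.95 it falls from 19.0 to 0.859 / 0.05 = 17.2 at q = 20%.

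As a cross-check, hold the confirmed total at 160 and let a fraction f of it be mislabelled. Observed sensitivity is then (1 − f) × Se + f × (1 − Sp). For Se = Sp = 0.95 the target is lost at f = 0.05, which is 8 patients.

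**Comparison C.** The article does not give the number of non-transmural cases. If it were 80 (assumed), the mislabelled share of that arm would be k / (80 + k): 4.5 / 84.5 = 5%, 9 / 89 = 10%, 18 / 98 = 18%. If non-ischaemic patients have lower biomarker values than true non-transmural cases, separation from transmural AMI is flattered. If their other illness raises the values, separation is blurred. The direction is not known in advance.

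**Comparison A.** The transmural arm should be almost untouched. The control group loses k patients (90 falls to 85.5, 81 or 72), which costs precision. It biases specificity only if those who leave test differently from those who stay.

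**The case against.** The definition is a reasoned choice. The Background calls CT angiography the gold standard for occlusive AMI and says NOMI has less distinctive CT signs, which explains why only NOMI needs endoscopy, surgery or autopsy throughout. The exclusion of purely chronic disease and investigator validation can both remove the patient described. An old stenosis without evident fresh thrombus or embolus may be classed as unclear and so reach the committee. The article is a condensed text, and adjudication detail may sit in the full protocol or in the case report form in Additional File 1, which is not shown. A stricter rule also carries a risk: early and acute-on-chronic cases, revascularised without surgery or endoscopy, could be pushed out of the non-transmural group that comparison C needs.

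Much of this stands. It rules out saying that such patients will always be counted, and it argues against a hard reclassification rule. It does not remove the gap. The reference standard is printed here, this patient meets it as worded, and none of the safeguards says how an acute event is distinguished from unrelated pain.

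A reader might also infer that acute symptoms are themselves the entry criterion. They are not. Entry is the decision to investigate, and the listed symptoms are its main but open-ended basis.

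**Conclusion.** As worded, the rule allows a patient with an old total or subtotal occlusion and acute symptoms from another cause to be counted as confirmed AMI. How often this would happen cannot be derived from the documents.

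The figures for comparison B are an upper bound for each assumed share, because they let every such patient past every safeguard. At 5% both scenarios still meet LR- < 0.1. At 10% both miss it. If the true performance is near the target, about five to eight mislabelled patients are enough to change that secondary conclusion.

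A reader might infer that the primary result is undermined. The documents do not support this. Such patients would most likely be labelled non-transmural, so comparison A is touched only through its control group. The weight falls on comparison B, on comparison C with uncertain direction, and on the score. The point justifies a change of wording and a sensitivity analysis, not a redesign.

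**What to change.** In the definition of confirmed AMI, extend the existing steering committee review to occlusive cases confirmed by imaging and symptoms alone when either of these applies:
- the imaging neither describes the occlusion as acute nor shows bowel ischaemia; or
- another final diagnosis explains the symptoms.

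The committee should decide blind to the biomarker results. Do not reclassify these cases automatically, so that true early and acute-on-chronic cases are kept. Report comparisons A to C with and without these cases as a sensitivity analysis.

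The cost is a wording change, one or two items on the case report form (imaging description, final alternative diagnosis) if they are not already there, a few more committee reviews, and possibly slightly fewer than 160 confirmed cases. Sampling and patient care do not change.

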Statistical analysis will be performed with R Statistical Software 4.3.2 (R Core Team, Vienna, Austria, 2023). Data will be described in number (%), median (interquartile range, IQR) or mean (standard deviation, SD) as appropriate. Kolmogorov–Smirnov test will be used for data distribution normality testing. Analyses for confirmed transmural AMI vs suspected but not confirmed AMI (comparison A – primary outcome), confirmed AMI of any stage vs suspected but not confirmed AMI (comparison B – secondary outcome) and transmural vs non-transmural AMI (comparison C – secondary outcome) will be performed in different measurement time points. Each biomarker will be described at each measurement point for all comparisons (A, B and C), using Student’s t-test or Wilcoxon rank-sum test as appropriate. For all biomarkers showing a *p*-value < 0.05 in at least one measurement point in univariate analysis, the area under the receiver operating curve (ROC) calculation will be performed. We will do this separately for comparisons A, B and C and identify optimal cut-off values for each biomarker based on maximum value of the Youden index [13]. All measurement time points before any treatment of AMI (1,2,3,6,8) will be pooled and AUROC analysis will be performed to identify the best cut-offs also for pooled data for each biomarker. Sensitivity, specificity, positive predictive value (PPV), negative predictive value (NPV) and likelihood ratios (LR) with 95% CI-s will be reported. Positive likelihood ratio (LR +) > 10 and negative likelihood ratio (LR-) < 0.1 will be considered high diagnostic accuracy and LR +  > 5 and LR- < 0.2 as moderate diagnostic accuracy. All biomarkers with at least moderate accuracy will be entered as binary covariates (using the best cut-offs previously found in the AUROC analyses resulting in highest AUC) into the multivariable stepwise logistic regression analysis (both directions) to identify the best combination of biomarkers discriminating between transmural AMI and no AMI based on Akaike information criterion (AIC). Analogical approach will be used for comparisons B and C. The best models will be applied to subgroup analyses in different sub-types of AMI. If the best models selected as described previously, do not perform well at different measurement time points or in different subtypes of AMI, additional analyses will be undertaken testing alternative combinations. We will present the best models for each comparison and for each subtype separately and will use them to construct a practical score that can be used to distinguish between no AMI, non-transmural AMI and transmural AMI (Table 3). If the different cut-offs from different models contradict (for example cut-off for non-transmural AMI vs transmural AMI is lower than the cutoff for no AMI vs AMI) additional analyses will be performed and more appropriate cut-offs will be found considering acceptable sensitivity and specificity from previous AUROC analyses. This approach will be compared to decision tree approach and if the decision tree accuracy is higher than the score’s accuracy, a decision tree will be preferred. The accuracy of the decision tree and the score will be calculated as proportion of correct predictions.

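### NOMI that is suspected on imaging but never verified stays in the control group that comparisons A and B label *no AMI*, which may lower observed specificity and LR+

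*Protocol article*

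**What the plan says.** Under Definitions, in the part on confirmed AMI, the route for the non-occlusive subtype is "Non-occlusive mesenteric ischaemia confirmed by either endoscopy, surgery or autopsy". The next sentence deals with patients who have only imaging: "A suspicion of NOMI in CT, MRI or angiography without being confirmed by any of these methods remains a suspicion of AMI". The same part sends every case lacking definitive confirmation to the steering committee, which settles its category with the site.

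The Statistical analysis section then defines the primary contrast: "Analyses for confirmed transmural AMI vs suspected but not confirmed AMI (comparison A – primary outcome". Comparison B uses the same controls.

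Elsewhere the controls have a different name. The primary objective seeks a combination that "distinguishes patients with transmural AMI from patients with no AMI", and the secondary objective for comparison B uses the same label. The modelling step looks for the "best combination of biomarkers discriminating between transmural AMI and no AMI". The first column of the score in Table 3 is also headed *no AMI*.

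The planned numbers are 160 patients with confirmed AMI, 40 of them with NOMI, and 90 with suspected but unconfirmed AMI. The primary target is LR+ above 10 with LR− below 0.1.

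**The concern.** Unconfirmed is not the same as ruled out. A patient whose imaging raised NOMI, and who had no endoscopy, surgery or autopsy, is a control under the definition and is disease-free under the label. Such patients can be expected. The Background notes that "non-occlusive AMI (NOMI) has less distinctive CT signs", the Definitions place suspected NOMI in critically ill patients, and Study procedures leaves all diagnostics to local practice, so the study does not itself require verification.

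If some of these patients do have NOMI, a biomarker combination that correctly flags them is charged with false positives. Observed specificity and LR+ fall, while LR− barely moves. The study's success criterion is a fixed LR+ threshold and there are only 90 controls, so a modest number of such patients could decide whether the primary or the first secondary objective is met. The same controls also serve to screen single biomarkers (LR+ above 5 and LR− below 0.2) before they enter the multivariable model.

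**Working it through.** **Inputs from the protocol.** There are 90 planned controls, and the target is LR+ > 10 and LR− < 0.1. The 90 comes from a recruitment forecast, not a power calculation. Applying the stated losses of 5%, 10% and 15% in sequence gives a factor of 0.95 × 0.90 × 0.85 = 0.727. Then 220 × 0.727 = 159.9 confirmed (plan: 160), 120 × 0.727 = 87.2 suspected (plan: 90), and 340 × 0.727 = 247.1 in total (plan: 250). The plan's figure of 90 is used below.

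**Assumptions (not in the documents).** True sensitivity is 0.92 and true specificity 0.95. The number m of controls who truly have NOMI is varied as 0, 5, 10 and 15. Their test-positive rate q is either 0.92 (they behave like confirmed cases) or 0.46 (half as often).

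**Formulas.**
- Observed false-positive rate: FPR = [(90 − m) × 0.05 + m × q] / 90
- LR+ = 0.92 / FPR
- LR− = 0.08 / (1 − FPR)

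**Example, m = 5 and q = 0.92.** FPR = (85 × 0.05 + 5 × 0.92) / 90 = (4.25 + 4.60) / 90 = 0.0983. LR+ = 0.92 / 0.0983 = 9.4.

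| m of 90 | q | FPR | Specificity | LR+ | LR− |
|---|---|---|---|---|---|
| 0 | – | 0.050 | 0.950 | 18.4 | 0.084 |
| 5 | 0.92 | 0.098 | 0.902 | 9.4 | 0.089 |
| 10 | 0.92 | 0.147 | 0.853 | 6.3 | 0.094 |
| 15 | 0.92 | 0.195 | 0.805 | 4.7 | 0.099 |
| 5 | 0.46 | 0.073 | 0.927 | 12.6 | 0.086 |
| 10 | 0.46 | 0.096 | 0.904 | 9.6 | 0.088 |
| 15 | 0.46 | 0.118 | 0.882 | 7.8 | 0.091 |

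**Break-even.** LR+ = 10 requires FPR = 0.092, that is 8.28 positives among 90 controls. Of these, 4.5 would be expected without misfiling. So m = 3.78 / (0.92 − 0.05) = 4.3 when q = 0.92, and m = 3.78 / (0.46 − 0.05) = 9.2 when q = 0.46. The target is lost from 5 and from 10 patients respectively. If q were 0.05, the rate in true controls, nothing would change.

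**Ceiling.** A perfect test that is also positive in every misfiled case has LR+ = 1 / (m/90), which is exactly 10.0 at m = 9. From there on no test could exceed 10.

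**Which q fits which comparison.** In A the cases are transmural. Unverified NOMI had no surgical or autopsy confirmation and is probably often non-transmural, so the lower positivity is the more plausible row. In B any stage counts as disease, so the higher positivity is more relevant.

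**The case against.** The case on the other side has real force in several places.

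- *CT suspicion is not disease.* The rule concerns a suspicion, and weak CT signs are themselves a reason not to count such patients as AMI. This stands: a reader might infer that these patients are all probable AMI, but the text supports only that some may be. The calculation treats m as the number with true NOMI, which is unknown.
- *The steering committee reviews these cases.* It may reassign individual patients. Its working criteria may be set out in a fuller document, so their absence from an article is not held against the plan. The definition and the label, however, are both fixed in the article, and they do not agree.
- *The bias is conservative.* It lowers LR+, so it does not favour a claim of success. That is correct, but the study could then discard a combination that works, or report too low a specificity for a score meant for clinical use.
- *Excluding hard cases flatters the test.* Also correct. Cleaner controls can inflate specificity, so exclusion should not simply replace the current analysis.

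Three stronger readings are tempting but not supported:

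- *Late-found strangulation.* The clause beginning "If a SBO was identified as a cause of AMI only after including the patient in the study" may suggest that these patients have no category to go to. The section on subtypes sends cases with another specific mechanism to the committee for allocation and for mention in the final report. Obstruction verified at first assessment is excluded.
- *Laboratory results in the reference standard.* The wording "without any laboratory abnormalities is not sufficient to confirm AMI" applies to imaging findings in patients without symptoms, who should be few because enrolment rests on clinical suspicion. The central biomarkers are frozen and shipped in two batches, so at most locally measured markers could play a part.
- *Youden cut-offs pushed upward.* If misfiled cases are distributed like confirmed cases and make up a share c of controls, observed J = Sens − [(1 − c) × FPR + c × Sens] = (1 − c) × (Sens − FPR), with FPR here the true false-positive rate. J shrinks by the same factor at every cut-off, so its maximum does not move. A shift would need a different distribution, and the documents give none.

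**Conclusion.** The point holds as a mismatch between a stated definition and a stated label. Imaging-suspected, unverified NOMI remains among the controls of A and B, and those controls are called *no AMI*. The direction of the effect is clear if some of these patients have NOMI and test positive more often than true controls: specificity and LR+ fall, and LR− changes little.

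The size is conditional. Under the assumed accuracy (0.92 and 0.95), the LR+ target of more than 10 is lost from about 5 of 90 controls if they test positive like confirmed cases, and from about 10 of 90 if half as often. The second figure is the fairer guide for the primary comparison. The documents do not show that either number will be reached, so it would be wrong to conclude that the primary objective will fail. What follows is that a result near the threshold could not be interpreted without knowing how many controls were indeterminate.

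**What to change.** 1. Have the steering committee classify each unconfirmed case, without sight of biomarker results, as AMI ruled out or indeterminate. Imaging-suspected NOMI that was never verified belongs in the indeterminate group.
2. Report the number of indeterminate cases.
3. Report comparisons A and B twice: with indeterminate cases kept as controls, as now, and with them excluded. For B, add a third run that counts them as AMI.
4. Use the label *no AMI* only for the ruled-out group. Otherwise name the comparator as unconfirmed.

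**Cost.** This needs one more adjudication category and a few repeat analyses on data already collected. Precision suffers little: at a specificity of 0.95 the 95% half-width is 1.96 × √(0.95 × 0.05 / n), which is 4.5 points at n = 90, 4.6 at n = 85 and 4.8 at n = 80. The run without indeterminate cases may be optimistic about specificity, which is why both results should be shown side by side.
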